#### Sociodemographic characteristics

Data on the following background and sociodemographic characteristics will be collected: (1) sex; (2) relationship status; (3) having children or not; (4) Swedish county of residence; (5) living in urban or rural area; (6) level of education; (7) employment status; (8) place of birth; (9) mother’s place of birth; (10) father’s place of birth; and (11) childhood negative events (bullying, family conflict, lack of affection).

#### Clinical cancer-related characteristics

The following clinical characteristics related to cancer will be collected: (1) type of cancer (leukaemia, central nervous system tumour, solid tumour, lymphoma or other malignancy); (2) number of relapses (0, 1 or >1); and (3) current late effects of cancer (multiple choice listed).

#### Actual help-seeking behaviour

The following items will be used to examine actual help-seeking behaviour: (1) emotional health difficulties related to the childhood cancer experience; (2) the type of support received by those who accessed support in the past 6 months and/or in the past (not including the past 6 months): (a) face-to-face individual or group support from mental health professional; (b) face-to-face support from a general practitioner/family doctor; (c) technology-administered mental health support (eg, online therapy programme, smartphone application, video conferencing or teleconferencing); (d) technology-administered support from a general practitioner/family doctor (eg, online, video conferencing or teleconferencing); (e) social media support group; (f) phone help-line; (g) family, partner or friend/s; (h) religious leader; and (i) other. Type of support will be categorised into: (1) face-to-face professional support; (2) technology-administered professional support; and (3) informal support (social media support group, family, partner, friends and religious leader). Those who sought support for mental health difficulties in the past 6 months and received support from a health professional either face-to-face or technology assisted will be defined as ‘help-seeking’.^70^

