E-mental health (e-MH), defined as the provision of psychological support via information technology and new media (eg, online, smartphone applications, video conferencing),^25^ may represent a solution to reduce the mental health treatment gap.^26^ One example of e-MH is internet-administered cognitive behavioural therapy (ICBT). ICBT has been found to be effective for a range of common mental health difficulties, such as depression and anxiety,^27^ including for young adult populations^28^ and has been found to be as effective as traditional face-to-face CBT.^29^ e-MH interventions may help overcome practical barriers associated with accessing traditional face-to-face psychological support (eg, geographical, financial and time-related barriers)^30^ that have been observed within the AYACCS population.^31^ Furthermore, e-MH is associated with anonymity and privacy^32^ thus potentially overcoming barriers associated with public stigma. Indeed, research has identified that the provision of e-MH interventions may be a potential solution for the AYACCS population.^33–38^ However, research examining e-MH support for an AYACCS population has encountered challenges with recruitment, attrition, and internet use.^34 38^ For example, one study examining the feasibility and acceptability of e-MH recruited only 28 participants over a 12-month period and experienced almost 30% attrition.^38^ Another feasibility study of e-MH for adolescents and young adults who had experienced cancer during the adolescent period recruited only 6 participants from a total of 320 potential participants invited into the study, and experienced a 100% attrition rate.^34^ Indeed, a recent review of e-Health interventions for AYACCS concluded that engaging the population was challenging, and there is currently a lack of literature concerning how to better engage the population.^36^ However, challenges with recruitment, attrition and internet use are common in the field of e-MH research.^39–41^ Potentially, challenges with recruitment, attrition and internet use may be related to help-seeking behaviour and the acceptability of e-MH for the population.

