#### Attitudes towards internet-administered interventions

The 17-item e-Therapy Attitudes Measure (ETAM)^71 72^ will be adopted to measure attitudes towards internet-administered interventions, however, for the purpose of the present study one item concerning health insurance companies was excluded due to not being relevant in the Swedish context. The questionnaire begins with definitions of three types of internet-administered interventions: (1) unguided internet-administered self-help programmes; (2) therapist-guided internet-administered self-help programmes; and (3) psychological therapy delivered via video conferencing. Subsequently, respondents are required to state which type of internet-administered intervention they would prefer, or state if they would not use internet-administered treatment at all. Subsequently, the ETAM is presented and explores attitudes towards internet-administered interventions. Specifically, respondents are instructed to state whether they agree with each statement on a 5-point rating scale ranging from 0 (‘strongly disagree’) to 4 (‘strongly agree’) and are asked to rate items considering therapist-guided internet-administered self-help programmes. The ETAM has been demonstrated to have good internal-consistency reliability (α=0.89).^72^

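### Response option (c) of the help-seeking item does not record whether a professional was involved, so some technology-only users may be counted as professionally helped; phone help-line and other have no category

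*Protocol article*

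**What the plan says.** All of this is in the protocol article.

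- **Outcome definition** (Actual help-seeking behaviour). Of those who sought support in the past 6 months, respondents who "received support from a health professional either face-to-face or technology assisted will be defined as ‘help-seeking". This is the dependent variable for the first research question.
- **Options that name a professional.** (a) "face-to-face individual or group support from mental health professional"; (b) "face-to-face support from a general practitioner/family doctor"; (d) "technology-administered support from a general practitioner/family doctor (eg, online, video conferencing or teleconferencing".
- **Option (c).** "technology-administered mental health support (eg, online therapy programme, smartphone application, video conferencing or teleconferencing". No provider is named.
- **Categories.** There are three: face-to-face professional, technology-administered professional, and "informal support (social media support group, family, partner, friends and religious leader". Only the informal category lists its members. Phone help-line (f) and other (i) are offered as responses but named in no category.
- **Table 1.** The types of support are formal, technology and informal, which sets technology apart from formal.
- **Number of items.** Survey items gives this section two items. No follow-up question about the provider is described.
- **Attitudes towards internet-administered interventions.** Here the survey does separate formats: "unguided internet-administered self-help programmes; (2) therapist-guided internet-administered self-help programmes", with video therapy as a third.

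**The concern.** The outcome turns on who gave the support, and option (c) asks only how it was delivered. Someone who used a self-help app with no professional involved and someone who had weekly video sessions with a psychologist give the same answer. Since (c) is not among the listed informal sources and the only technology category is called professional, the natural reading codes both as help-seeking.

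The logistic regressions for the first research question use this variable, so false positives in it alter the odds ratios. The protocol itself gives a reason why app use and professional care might relate differently to a predictor. The Introduction notes that "e-MH is associated with anonymity and privacy" and that this could get round barriers due to public stigma, and public stigma is one of the Table 1 predictors.

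Most missing coding rules can be written later in an analysis plan. This one cannot, because the item does not collect the provider information that such a rule would need.

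**Working it through.** **Step 1: map the nine options to the definition.**

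| Option | Professional named? | Category in the text | Status if the only support |
|---|---|---|---|
| (a), (b) | yes | face-to-face professional | help-seeking |
| (d) | yes | technology professional, by its wording | help-seeking |
| (e), (g), (h) | no | informal, listed | not help-seeking |
| (c) | not recorded | none listed; technology professional by elimination | undetermined |
| (f), (i) | not recorded | none | undetermined |

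Six of nine options can be classified with certainty and three cannot. Anyone who also ticks (a), (b) or (d) is help-seeking whatever else is ticked. Status is therefore open only for those reporting (c), (f) or (i) without (a), (b) or (d).

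**Step 2: how much could (c) matter?** The protocol states no figure to reproduce here. Only n=365 is taken from it (Sample size estimation). *Assumed*: 20% truly received professional help, a 50/50 binary predictor (high or low stigma, 182.5 each), and a true odds ratio (OR) of 0.50 for high against low stigma.

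- Solving (p_L + p_H)/2 = 0.20 with OR 0.50 gives p_L = 0.254 and p_H = 0.146.
- Let a be the share of those without professional help who used only an app and are coded help-seeking. The coded rate is q = p + (1 − p)a.
- Observed OR = [q_H/(1 − q_H)] / [q_L/(1 − q_L)].
- Power = Φ(|ln OR|/SE − 1.96), with SE² = Σ 1/[182.5 q(1 − q)] over the two groups.

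With a = 0 the OR is 0.50 and power is 0.73.

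Example, a = 0.06 in both groups: q_L = 0.254 + 0.746 × 0.06 = 0.299 and q_H = 0.146 + 0.854 × 0.06 = 0.197. The OR is (0.197/0.803)/(0.299/0.701) = 0.57, and power is 0.61. False events are 0.06 × 292 = 17.5, and 17.5/(73 + 17.5) is 19% of coded events.

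| App-only share (assumed) | Relation of app-only use to high stigma (assumed) | Observed OR | Power |
|---|---|---|---|
| 1% | none | 0.51 | 0.71 |
| 2% | none | 0.53 | 0.69 |
| 6% | none | 0.57 | 0.61 |
| 3% | opposite to professional care (OR 2) | 0.59 | 0.53 |
| 6% | opposite (OR 2) | 0.68 | 0.35 |
| 10% | opposite (OR 2) | 0.78 | 0.18 |
| 6% | same as professional care (OR 0.5) | 0.48 | 0.83 |

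The result runs from negligible, through material attenuation, to slight exaggeration with higher power. The (f) and (i) part is not quantified, because the text does not fix which way those respondents are coded.

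**The case against.** Three stronger readings are tempting, and the document supports none of them.

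1. *Professional support cannot be established from this survey at all.* Step 1 shows otherwise: (a), (b) and (d) settle the matter one way, and (e), (g) and (h) alone settle it the other way.
2. *The misclassification is known to be non-random and cancels the stigma association.* The Introduction says only that e-mental health might overcome stigma barriers; it gives no direction or size for app-only use. It also cites a study with weaker e-mental health use among young people with negative childhood experiences, so technology use need not compensate for barriers. If app-only use follows the same pattern as professional care, the association is not weakened.
3. *Help-line users are wrongly put in the reference group.* The text does not say so. A help-line is itself delivered by technology, and its allocation is simply unstated.

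It can also fairly be said that this is an article summarising a questionnaire it does not reproduce, that the members of the technology professional category are not listed, and that option (c) does not itself mention unguided use. Coding rules for help-line and other, and free text under other, are details that a fuller document can supply. That largely disposes of (f) and (i) as anything beyond a coding gap, since both are already separate responses.

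It does not dispose of (c). The option's examples include an app and an online programme, so its wording admits use without a professional. No later rule can recover what the item did not ask.

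**Conclusion.** The point holds in a limited form. The outcome requires a health professional, option (c) does not record whether there was one, and the only technology category is labelled professional. Respondents whose only support in the past 6 months was (c) may be counted as help-seeking without any professional contact, and the items as described cannot separate them later. Help-line and other lack a category, which is a smaller gap that a coding rule can close.

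The effect on the odds ratios is of unknown size and direction, because the documents give no rates for these options. The figures above rest on assumed prevalence, odds ratio and app use, and show a range, not an expected loss. The case for change is that it is cheap before data collection and cannot be made good from the described data afterwards.

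**What to change.** Before the pilot testing described under Patient and public involvement:

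1. Split (c) into (c1), technology-administered support with contact with a therapist or other health professional (video, telephone or guided programme), and (c2), a programme or app used without such contact. The attitudes section already draws this distinction.
2. Count (a), (b), (c1) and (d) as help-seeking. Report (c2) separately.
3. State in advance where (f) and (i) go. Take free text for other and code it blind to the predictors. Add a sensitivity analysis that reclassifies respondents reporting only (f) or (i). Respondents may not know who staffs a help-line, so any fixed allocation of (f) is debatable and the sensitivity analysis is the safeguard.
4. Bring the Table 1 categories into line with those under Actual help-seeking behaviour.

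The cost is one or two extra response options within an existing item, slightly fewer events because app-only users no longer count, and slightly less comparability with the cited study from which the definition is taken.

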#### Attitudes towards internet-administered interventions

The 17-item e-Therapy Attitudes Measure (ETAM)^71 72^ will be adopted to measure attitudes towards internet-administered interventions, however, for the purpose of the present study one item concerning health insurance companies was excluded due to not being relevant in the Swedish context. The questionnaire begins with definitions of three types of internet-administered interventions: (1) unguided internet-administered self-help programmes; (2) therapist-guided internet-administered self-help programmes; and (3) psychological therapy delivered via video conferencing. Subsequently, respondents are required to state which type of internet-administered intervention they would prefer, or state if they would not use internet-administered treatment at all. Subsequently, the ETAM is presented and explores attitudes towards internet-administered interventions. Specifically, respondents are instructed to state whether they agree with each statement on a 5-point rating scale ranging from 0 (‘strongly disagree’) to 4 (‘strongly agree’) and are asked to rate items considering therapist-guided internet-administered self-help programmes. The ETAM has been demonstrated to have good internal-consistency reliability (α=0.89).^72^

#### Symptoms of depression, anxiety and stress

The Swedish version^73^ of the (7-item depression, 7-item anxiety and 7-item stress subscales) Depression Anxiety and Stress Scale (DASS-21)^74 75^ will be adopted to examine symptoms of depression, anxiety and stress. The DASS-21 has adequate psychometric properties^76^ and satisfactory test–retest reliability,^77^ with support for the factor structure and convergent validity of the Swedish version.^73^

#### Stigma of mental illness

The 5-item Stigma Scale for Receiving Psychological Help (SSRPH)^78^ will be adopted to measure public stigma, that is, negative perceptions concerning the receipt of mental health services. The measure has demonstrated to be reliable and valid in studies with young adults^79^ and adolescents.^80^ Respondents rate degrees of agreement using a 4-point Likert scale ranging from 0 (‘strongly disagree’) to 3 (‘strongly agree’), with a higher score representing a higher level of stigma.

#### Social support

The 12-item Interpersonal Support Evaluation List (ISEL-12)^81^ will be adopted to examine perceptions of social support. Responses are provided on a 4-point Likert scale, ranging from 1 (‘definitely false’) to 4 (‘definitely true’).

#### Mental health literacy

A 26-item multicomponent MHL measure, demonstrated to have good internal consistency (of 0.83 of the KR-20 coefficient=0.83),^82^ will be adopted to assess knowledge-oriented, beliefs-oriented and resource-oriented MHL. The first 22 items examining knowledge-orientated and beliefs-orientated MHL are answered on a 5-point Likert scale ranging from 0 (‘strongly disagree’) to 4 (‘strongly agree’) and the option of “I don’t know”. The response format for the final four items, examining resource-orientated MHL, is ‘yes’ or ‘no’.

### Translation of English language outcome measurements into Swedish

Currently, there are no Swedish versions of the following outcome measurements: (1) ETAM, (3) SSRPH, (4) ISEL, and (5) MLH. The following steps will be taken to translate: (1) one clinical psychologist, native Swedish speaker with advanced knowledge of English, will translate each outcome measurement to Swedish and (2) translations will be reviewed, discussed and revised with a research assistant in our study team who is a native Swedish speaker with advanced knowledge of English. Professional back translation to English and discussion with the original author is out of scope for the present study due to time and resource limitations. However, permission to translate outcome measurements to Swedish will be sought.

### Embedded qualitative interview study

An embedded qualitative interview study will be conducted to explore: (1) perceived need for mental health support; (2) past experience of receiving mental health support; (3) preferences for support; and (4) barriers and facilitators to help-seeking. As this study will be examining mental health help-seeking, only respondents meeting the following criteria will be invited into the study: (1) self-reported current and/or past experience of mental health difficulties during life time (yes) and/or (2) DASS-21 depression score ≥5 and/or (3) DASS-21 anxiety score ≥4 and/or DASS-21 stress score ≥8. Respondents will be provided with full study information and an online consent form. Respondents meeting these criteria will be invited consecutively until thematic data saturation is met.^83 84^ As the decision concerning whether data saturation has been met is made during the analytic process, it is difficult to determine the number of interviews a priori; however, we may anticipate interviewing approximately 20–30 participants.^85^ As we are interested in both barriers and facilitators to seeking help, we will endeavour to interview participants classified as help-seekers and non-help-seekers. For participants who send the consent form and reply slip via the post, those meeting the inclusion criteria will be contacted by the study team to provide full study information and obtain informed consent. Interviews will be conducted either via the telephone or a secure video conferencing system on the U-CARE portal. Interviews will be audio recorded with informed consent and transcribed with personal information removed. Participants will be informed about the recording and give approval when giving consent to the interview. An interview guide will be developed, consisting of open-ended questions, structured around the third research objective covering the following topics: (1) perceived need for mental health support; (2) past experience of receiving mental health support (formal/informal, cancer-specific/non-cancer-specific); (3) preferences for support (eg, type of support, emotional difficulties to be target and intervention content areas); and (4) barriers and facilitators to help-seeking behaviour (eg, perceived attitudes of peers, knowledge/information, economic resources, geographical location, stigma). The interview guide will be partially informed by emerging survey results and findings from studies examining help-seeking behaviour in young adults.^32 42 50 70^ Interviews are estimated to last 45–90 min.

### Data analysis

#### Statistical analysis

All statistical analyses will be conducted using SPSS V.26.0 software (IBM SPSS Statistics for Windows, 2019, Armonk, New York, USA). Sociodemographic and clinical characteristics will be presented with descriptive statistics. The potential association between predicting factors as informed by Andersen’s behavioural model of health services use (predisposing, enabling, environmental, and need-related factors) and the dependent variable help-seeking behaviour, for example, receipt of mental health support in the past 6 months will be examined using univariable and multivariable logistic regressions.^70^ The non-help-seeking group will used as the reference group.^70^ First, univariable analyses will be conducted for each predictor separately. Variance inflation factor will be used to examine multicollinearity prior to the regression analysis. A multivariable logistic regression will be performed using stepwise manual backward selection procedure. All predictor variables will initially be included, and non-significant predictors will be eliminated with only variables significantly related to the dependent variable (p<0.05) retained. For both the univariable and multivariable logistic regressions, ORs will be presented, alongside 95% CIs, and p values. Given the heterogeneous nature of the study population, subgroup analysis will be performed by stratifying the population by age and sex. The same method of modelling will be used for the subgroup analyses for age (15–19 years vs 20–29 years vs 30–39 years) and sex (male vs female). The subgroup analysis will be exploratory and with results used to inform subsequent studies.

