### Survey items

An online and paper-based survey, consisting of 98 items in Swedish. The survey comprises eight subsections: (1) sociodemographic characteristics (11 items); (2) clinical cancer-related characteristics (3 items); (3) actual help-seeking behaviour (2 items); (4) attitudes towards internet-administered interventions (17 items); (5) stigma of mental illness (5 items); (6) MHL (26 items); (7) social support (12 items); and (8) current symptoms of depression, anxiety and stress (21 items). One open question at the end of the survey offers and opportunity to provide any further information concerning emotional distress and preferences for support after childhood cancer. Potential predisposing, enabling, environmental, and need-related factors examined with the survey are summarised in table 1.

**Table 1 T1:** Factors to be examined as per Andersen’s behavioural model of health services use

Andersen’s behavioural model of health services use	Factors*
Predisposing	Sex (male/female/other) Age (16–24/25–39) Time since first cancer treatment (years) Place of birth (born in Sweden/born outside of Sweden) Childhood negative events (yes/no) Level of education (≤upper secondary school/>upper secondary school) Public stigma (Stigma Scale for Receiving Psychological Help) Mental health literacy
Enabling	Type of cancer (leukaemia/central nervous system tumour/solid tumour/lymphoma/other) Relationship status Employment status (yes/no/studying) Social support (12-item Interpersonal Support Evaluation List)
Need-related	Symptoms of depression (DASS-21 depression subscale) Symptoms of anxiety (DASS-21 anxiety subscale) Symptoms of stress (DASS-21 stress subscale) Self-reported experience of mental health difficulties in past 6 months (yes/no)
Environmental	Region of Sweden (south/mid/north) Rural or urban area
Actual help-seeking behaviour (dependent variable)	Receipt of mental health support in the past 6 months Type of mental health support received in the past 6 months (formal/technology/informal)

*Outcomes selected informed by previous research.^32 42 50 70^

DASS-21, Depression Anxiety and Stress Scale.

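### Backward elimination at p<0.05 from 18 theory-specified predictors gives odds ratios biased away from 1 for retained factors, weakened confidence intervals and no adjusted estimate for dropped factors

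*Protocol article*

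**What the plan says.** The Statistical analysis section of the protocol article first fits a univariable logistic regression for each predictor and checks variance inflation factors. It then states: "A multivariable logistic regression will be performed using stepwise manual backward selection procedure". All predictors enter at the start, and "non-significant predictors will be eliminated with only variables significantly related to the dependent variable (p<0.05) retained". On reporting, it says: "For both the univariable and multivariable logistic regressions, ORs will be presented, alongside 95% CIs, and p values". It mentions no shrinkage, resampling of the selection process or caution about inference after selection.

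The candidates are in Table 1 under Survey items, grouped as predisposing, enabling, need-related and environmental. Several have more than two levels, for example "Type of cancer (leukaemia/central nervous system tumour/solid tumour/lymphoma/other".

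Only the age and sex subgroup analyses are called exploratory, and they repeat the same modelling. The Discussion expects that the identified factors may point to targets for improving help-seeking.

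**The concern.** The first research question is one of inference on a list fixed in advance from theory: are these factors, in these four blocks, associated with help-seeking? Backward elimination is a screening tool. It conditions the reported estimates on having passed p<0.05, yet the ORs, CIs and p values are presented as if the final model had been chosen beforehand. Three things follow:

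- Retained ORs are pushed away from 1.
- CIs may not cover at 95%, above all where predictors are strongly correlated and compete for the same place in the model. The three DASS-21 subscales are the obvious candidates.
- A factor that is eliminated has no adjusted estimate at all, although the research question asks about it.

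At stake is the main multivariable table for the first aim, and the stability of the list of factors that later intervention work would draw on.

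**Working it through.** **Inputs from the protocol article.** n=365 (Sample size estimation); the Table 1 factors; elimination at p<0.05. The planned invitations reproduce: 365/0.40 = 912.5, so 913. The article gives no effect size or help-seeking rate, so 365 is taken as given and the rate is assumed.

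**Count of candidates.**
- Predisposing: 8 factors, 9 parameters (sex 2; age, time since treatment, birthplace, childhood events, education, stigma and mental health literacy 1 each).
- Enabling: 4 factors, 8 parameters (cancer type 4, relationship status 1, employment 2, social support 1).
- Need-related: 4 factors, 4 parameters (three DASS-21 subscales, self-reported difficulties).
- Environmental: 2 factors, 3 parameters (region 2, rural or urban 1).
- Total: 8+4+4+2 = 18 factors; 9+8+4+3 = 24 parameters. This is a minimum, taking relationship status as binary and literacy as one score.

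**Events per parameter** = 365 × rate / 24. At 10%: 36.5/24 = 1.5. At 20%: 73/24 = 3.0. At 30%: 109.5/24 = 4.6.

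**Simulation A (assumed).** n=365; 24 separately removable predictors; four true ORs of 1.40 per SD and 20 null; rates of 10–30%; pairwise correlation 0.2, with a variant in which three true predictors are correlated at 0.7.
- Average OR of a true factor when retained: 1.54–1.77 (about 1.59 at 20%, 1.77–1.78 at 10%). Full-model median over all runs: 1.43–1.49.
- Coverage of the nominal 95% CI given retention: about 90–93% at equal weak correlation (repeat runs ranged from 88% to 95%, lowest at the 10% rate), and 56–82% in the 0.7 variant. The full model covers at 93–95%.
- A true factor is dropped in 35% of runs at 20% help-seeking and 57% at 10%; about 25–60% over the scenarios.

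**Simulation B (assumed).** 18 factors with 24 parameters, multi-level factors removed as a whole; rates of 15%, 25% and 35%; six true factors with ORs of 1.3 to 3.0 (stigma protective); correlated DASS-21 subscales; 400 runs per scenario (error about 2.5 percentage points).
- Depression, true OR 1.30: 1.61–1.78 when retained, against a full-model median of 1.31–1.38. It is retained in 38–43% of runs, so dropped in 57–62%.
- Childhood events, true OR 1.50: 1.99–2.31 when retained.
- Coverage given retention: 67–82% for the two true DASS-21 subscales, 86–96% for the other true factors.

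**At least one false factor.** For k independent null factors the chance is 1 − 0.95^k: 60% for k=18, 51% for k=14, 46% for k=12.

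| Scenario | After elimination | Full model, each factor at 0.05 |
|---|---|---|
| A: 4 true, 20 null | 66–75% | 65–72% |
| B: all 18 null | 58–61% | 60–64% |
| B: 6 true, 12 null | 45–48% | 44–51% |

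Elimination makes little difference to this rate.

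**Block tests.** In scenario A, with one likelihood-ratio test per Andersen block, the chance of any false block claim was 18–27% at 0.05 each and 6–10% at 0.05/4 = 0.0125.

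**The case against.** The strongest reply is that much of the usual case against stepwise selection does not separate the plan from its alternative. A reader might infer that elimination is what makes a spurious factor likely, and that dropping it would cure this. The table above shows otherwise: the rate comes from many tests at 0.05, and picking significant factors off the full model gives about the same. That objection stands in full.

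The OR inflation is likewise an effect of looking only at significant factors. Restricted to p<0.05, the full model averaged 1.64 against 1.58 after elimination at 20% events, and 1.88 against 1.77 at 10%. This also stands. The gain from the full model is that all its estimates are shown, so the reader does not see only the selected ones.

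A reader might also infer that every CI in the table is badly wrong. For weakly correlated factors the loss is mild. The serious loss depends on an assumed strong correlation.

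The plan checks variance inflation factors and gives a univariable OR for every factor. The first describes collinearity but does not correct inference after selection. The second means that dropped factors keep an estimate, though not an adjusted one. Nor does the article say that dropped factors will be read as unassociated.

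Finally, the study is a cross-sectional survey that speaks of potential associations, disclaims causal conclusions and calls itself a first step. That lowers the stakes. It does not make a selected model the right answer to a question about named factors.

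**Conclusion.** The point holds as a should-fix. The plan fixes a selection procedure for a question that calls for estimates of all the pre-specified factors, and it reports the result without allowing for selection. Under the assumptions shown, a true OR of 1.40 is reported at about 1.5–1.8 when retained. Coverage given retention is about 90–93% for weakly correlated factors and about 55–82% for strongly correlated ones. True factors lose their adjusted estimate about 25–60% of the time.

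These sizes rest on assumed help-seeking rates, effect sizes and correlations, none of which the article gives. The direction of the OR bias and the loss of adjusted estimates do not depend on the exact values; the extent of the coverage loss does.

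The documents do not support the stronger reading that elimination will mostly produce a spurious factor. The chance is roughly 45–75%, depends on how many factors are real, falls below one half with six real factors of 18, and is a matter of multiplicity that the full model shares.

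**What to change.** - Make the full pre-specified Table 1 model the main multivariable result, and report every adjusted OR with its 95% CI. A Firth penalty with profile-likelihood CIs is preferable at about 1.5–4.6 events per parameter. Whether the named software version offers it needs checking.
- Answer the first research question with one likelihood-ratio test for each block (predisposing, enabling, environmental, need), adjusted for four tests, for example at 0.0125 each.
- State that single-factor p values are not confirmatory.
- Keep the univariable ORs as description.
- Label any backward-selected model exploratory, as the subgroup analyses already are.

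The cost is a few sentences of analysis text and a longer table, with no new data. CIs will be wider and fewer factors will be significant. The full model at so few events per parameter remains imprecise, and the wide CIs should be left to show that.
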